After obtaining data from the children, research assistants completed the school restroom inspection checklist, took photos of WaSH facilities, and interviewed school principals or representatives, inputting all data into the app. We obtained school administrative data, e.g., budget for maintenance and other operating expenses, from the DepEd. At the end of each workday, research assistants discussed their work with each other, shared lessons learned, and identified areas for improvement. Upon accessing an internet hotspot, we used the app to transmit anonymized data to a central database via cloud storage. Research assistants periodically checked uploaded data to verify the completeness of data upload and identify discrepant, missing, or duplicate data. When needed, appropriate remedial action was taken, e.g., re-training research assistants or clarifying instructions for children.

After completing baseline surveys, we assigned two schools to the control arm and 13 schools to the intervention arm (Figure 3). We purposefully assigned two schools to the control arm because one school had a school principal who directly asked us to participate in our previous observational study. The other school was integrated (offering all possible grade levels, from kindergarten to grade 12) and was the location where we had pilot-tested our survey instruments before the observational study. We randomly allocated schools in the intervention arm to one of four groups. One research assistant and the research supervisor conducted randomization in Microsoft^©^ Excel as follows: (1) In one column, we listed the names of the 13 schools in the intervention arm, with one row representing one school. (2) In another column, we listed the four intervention groups (A, B, C, and D), with one row representing one group. We previously determined how many schools would be allocated to each group (Table S1). (3) In a third column, we used Excel’s random number function and ranked the schools, assigning each school to either group A, B, C, or D (Table S1). Except for the research supervisor, all research assistants, study participants (children), school personnel, and parents were blinded to the assignment of schools to the intervention arm and subsequent random allocation to intervention groups A–D.

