#### 2.5.4. Follow-Up and Other Assessments

Eight months later, we conducted a follow-up assessment by implementing the same methodology (i.e., 4-part school-based survey) that we used at baseline (Figure S3) and measuring the same types of outcomes (e.g., children’s health literacy and nutrition status, handwashing prevalence, school restrooms’ WaSH adequacy, and schools’ WaSH policies). Nine months later (17 months after the first health education session), we conducted a household questionnaire for children (Table S5). Thus, we were able to assess risk factors at the individual-, school-, and home-levels (Table 2).

We expected the intervention to influence children’s knowledge, behavior, and health outcomes. We defined indicators of the intervention’s impact as changes in children’s primary and secondary outcomes. We measured the difference between outcomes from the eight-month follow-up and baseline. We compared differences between control and intervention arms. We collected samples for water quality testing from study schools and a separate sample of households (located in the school neighborhood) after post-intervention assessments, as previously reported [27].

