### 2.8. Statistical Analysis

Because our study contains multiple arms (1 control and 4 intervention arms), it is necessary to develop a strategy for conducting statistical analysis that takes into account the study’s 5 arms, parallel design, and unequal allocation ratio between control and intervention arms. We will use an adjustment method to control for type I error due to the study’s multiple-arm design. Because we simultaneously assessed multiple outcomes, we will need to adjust for a possible multiple comparisons effect. One possible adjustment method is the Benjamini–Hochberg procedure [42], which controls for the false discovery rate (10%). We used unequal allocation, making the intervention group larger than the control group, because we aimed to increase the precision of the intervention comparison. Also, we aimed to make the study more acceptable to study participants and researchers by decreasing the likelihood of being allocated to the control group and not receiving the intervention. Because we aim to know whether and how interventions differ, we will not use a single global test of significance, which would compare all groups simultaneously. Rather we will use a dose-response model to examine trends. We will conduct all analyses by using the originally assigned intervention status (i.e., intention to treat), comparing each intervention arm against the control arm.

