We will use generalized linear mixed models (GLMMs), which are appropriate for longitudinal data, to determine if the intervention was effective in improving our outcomes of interest. GLMMs are useful for measuring intervention impacts in complex datasets, i.e., when different types of variables (e.g., binary, continuous) are assessed at different time periods, particularly when assessments are made at the group- rather than individual-level. We will use GLMMs to estimate the effect of each intervention compared to the control group. To measure the intervention’s impact, we will estimate differences between pre- and post-intervention outcomes.

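### Pre-post change is the impact measure even for groups A-D, the only randomised comparison, where baseline adjustment would usually be more precise

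*Protocol article*

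**What the plan says.** Section 2.5.4 of the protocol article defines impact as change in the outcomes: "We measured the difference between outcomes from the eight-month follow-up and baseline". Section 2.8.2 repeats this in the paragraph on generalised linear mixed models (GLMMs): "we will estimate differences between pre- and post-intervention outcomes". Neither place treats any comparison differently from the others. The confounders that section 2.8.2 gives as examples are age, sex, and parental and home variables. The child's own baseline outcome is not among them.

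The contrasts that are written out are against control: "We compared differences between control and intervention arms" (section 2.5.4), "We will use GLMMs to estimate the effect of each intervention compared to the control group" (section 2.8.2) and "comparing each intervention arm against the control arm" (section 2.8). Comparing the packages with each other is nevertheless an aim. Section 2.1 gives comparison of the four packages as a purpose of the trial. Section 2.8 wants to learn whether and how the interventions differ, and says "Rather we will use a dose-response model to examine trends". The Conclusions speak of comparing impacts across volumes of health education.

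On allocation, section 2.5.3 says that after the baseline surveys "we assigned two schools to the control arm and 13 schools to the intervention arm". The two control schools were chosen on purpose. Chance entered only afterwards: "We randomly allocated schools in the intervention arm to one of four groups".

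**The concern.** Choosing between change and baseline adjustment is a real dilemma when groups are not randomised, because the two methods then rest on different assumptions about why the groups differed at the start. That dilemma applies to the control contrast here. It does not apply among A to D, whose schools were randomised after baseline. Expected baseline means are equal there, and adjusting follow-up for baseline is valid.

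Two things are at stake. The first is precision: 13 schools in four groups is about three per group, so little should be given away. The second is chance imbalance, which is likely with so few schools. A change score subtracts the whole baseline difference, although only a fraction of it is expected to persist to follow-up. A group that happens to start low then looks as if it improved more.

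**Working it through.** **What the article gives.** It states no standard deviation, intraclass correlation (ICC) or pre-post correlation, so there is no planned precision figure to reproduce for this comparison. Its one design figure is the target of 760 children. The Lynch formula with N = 2,059,447 and assumed p = 0.5, d = 0.05 and z = 1.96 gives 384.09, and 384.09 × 1.30 × 1.45 × 1.05 = 760.2, so that figure reproduces. It contains no correlation and does not bear on the choice of estimator.

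**Large-sample comparison.** With equal variance s² at both times and pre-post correlation r:

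- change score: variance 2s²(1 − r)
- baseline-adjusted follow-up: variance s²(1 − r²)
- ratio, adjusted to change: (1 + r)/2

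| r (assumed) | Variance ratio | Reduction in SE |
|---|---|---|
| 0.3 | 0.65 | 19.4% |
| 0.5 | 0.75 | 13.4% |
| 0.7 | 0.85 | 7.8% |
| 0.9 | 0.95 | 2.5% |
| 0.95 | 0.975 | 1.3% |

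**Cost of having 13 schools.** If the adjustment uses school means only, 13 schools in four groups leave 13 − 4 = 9 error degrees of freedom. Estimating the slope inflates the variance by 1 + 1/(9 − 2) = 8/7. The ratio becomes (8/7)(1 + r)/2: 0.86 at r = 0.5, 0.97 at 0.7, 1.03 at 0.8 and 1.09 at 0.9. The break-even is (1 + r)/2 = 7/8, so r = 0.75. For the width of a 95% interval, which also loses one degree of freedom, it is r = 0.68.

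**Simulation with schools as clusters.** Assumptions: groups of 3, 3, 3 and 4 schools (the real split is in Table S1, not shown), 47 children per school (703/15 = 46.9), and 4,000 runs per setting. The table gives the standard error of the D minus A difference, in outcome SDs.

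| ICC | School-level r | Child-level r | Change | Adjusted, child-level slope | Adjusted, school means |
|---|---|---|---|---|---|
| 0.05 | 0.5 | 0.5 | 0.199 | 0.174 | 0.187 |
| 0.05 | 0.8 | 0.5 | 0.152 | 0.149 | 0.151 |
| 0.05 | 0.95 | 0.95 | 0.064 | 0.063 | 0.067 |
| 0.10 | 0.9 | 0.5 | 0.152 | 0.165 | 0.154 |

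All three estimators were unbiased in every setting.

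**Why the last row reverses.** The variance of a school's baseline mean is 0.10 + 0.90/47 = 0.1191. Its covariance with the follow-up mean is 0.10 × 0.9 + 0.90 × 0.5/47 = 0.0996. The best slope for school means is therefore 0.0996/0.1191 = 0.84. A single slope pooled over children is 0.10 × 0.9 + 0.90 × 0.5 = 0.54. The change score's slope of 1 is nearer to 0.84 than 0.54 is. This is why the school and child levels need separate covariance. Even then the school-level slope must be learned from 13 schools: with the best slope known, the SE would be √[(1/3 + 1/4)(0.1191 − 0.0996²/0.1191)] = 0.145, but estimating it from school means gave 0.154.

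**Which outcomes have a usable baseline.** Table 2 dates the literacy questionnaire and the trial's anthropometry to June–July 2017 and February–March 2018. Handwashing was first observed in October 2017, while section 2.6 dates the intervention from June 2017. Adjusting for that first handwashing value would adjust for something the intervention may already have changed.

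**The case against.** The strongest reply is that the article never writes down a change-score comparison of A against B, C or D. Wherever it ties differences to a contrast, the contrast is with control, and for that contrast change is defensible. For A to D it names only a dose-response model, without an estimator. The proposed models are in Box S2 and the full ones are left to a forthcoming paper. A longitudinal GLMM also need not be a change-score analysis.

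Part of this stands. A reader might infer that the plan prescribes change scores for every contrast, but the text does not say so. Its application to A to D follows from three statements taken together: impact is defined as change, no exception is made, and impacts are to be compared across volumes. That inference is fair, but it is an inference. It is also right that a GLMM could be set up to recover the precision. The article does not say that it will be, and the one sentence on how impact is measured points to the pre-post difference.

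Two further readings go too far. One is that change scores are biased here; under randomisation they are not, and over-correction of chance imbalance is the same precision loss seen conditionally. The other is that adjustment is sure to be more precise; that is a large-sample result, and the last row of the simulation shows otherwise with 13 schools. Nor does the article support calling the literacy correlation moderate or the growth correlation high. Those are assumptions.

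**Conclusion.** The point holds as one of efficiency. For the only randomised comparison in the trial, the stated impact measure is usually less precise than an alternative that uses data already collected. If r is about 0.5 at both levels, the SE would be about 13% lower, in the large-sample formula and in the clustered simulation with child-level adjustment (0.174/0.199 = 0.87). At r of 0.9 or more the gain is about 1% to 3%. If schools keep their ranking far better than children do, it can vanish or turn into a loss (0.165 against 0.152 in the case shown). These sizes rest on assumed correlations, equal variances at both times and, for the simulation, an assumed ICC and split of schools. No wrong figure or bias is shown, and nothing here argues against change for the control contrast.

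**What to change.** Add to the analysis text, for contrasts among A to D and for the dose-response trend within A to D:

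- Analyse hygiene and handwashing literacy scores, height-for-age and BMI-for-age z-scores with a longitudinal mixed model that constrains baseline means to be equal across A to D, with separate school-level and child-level covariance. Alternatively, model follow-up on the child's baseline value, with the school's baseline mean if 13 schools can support it, and a school random effect.
- Report the change estimate for the same contrasts as a sensitivity analysis.
- Keep the change (difference-in-differences) estimate for contrasts with the two purposively assigned control schools.
- Do not apply the adjustment to observed handwashing, which has no pre-intervention value.

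The cost is wording only, since the article places the analyses in the future and the baseline values exist. The downsides are that two estimators appear, one per type of contrast, and that the gain is small for highly correlated outcomes. Before fitting, confirm how many children have both measurements: 703/756 is 93.0%, whereas section 2.3 states 86% retention, so the number of paired children is unclear.

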## 3. Discussion

Inadequate-WaSH-related diseases, specifically malnutrition, diarrhea, and STH infection, continue to be leading causes of child mortality and morbidity, particularly in LMICs [5,10,13]. One reason may be that many knowledge gaps still exist and hinder progress on school WaSH. For example, evidence about the relationship between health literacy and handwashing has been limited to adults [44] and older adolescents (age 16–19 years old) [45]. Little is known about how school WaSH impacts child growth and what kind of framework is needed to guide the development of child malnutrition prevention programs. Evidence is limited on which combinations of WaSH interventions could be implemented to achieve optimal health for urban poor children.

We have performed one of the most comprehensive assessments of school WaSH, children’s WaSH-related knowledge, attitudes, and practices (KAP), malnutrition, and risk factors at the individual-, school-, and home-levels. We will fill data gaps on school WaSH facilities, quantifying available resources and deficiencies and identifying areas for improvement. Data from our monitoring of school WaSH facilities will further the understanding contributed by previous studies that were limited by cross-sectional study designs [46,47]. To our knowledge, our study was the first school-based WaSH intervention trial to be conducted in multiple cities of Metro Manila using a common protocol, which will enable the comparability, transferability, and generalizability of the findings to similar LMIC settings. We will be among the first to report the impacts of school WaSH on malnutrition in an under-assessed population of children and younger adolescents (13–15 years old) from a tropical megacity in a LMIC. Our study will show how children’s physical growth could be improved by school-based WaSH interventions, providing key information for malnutrition prevention programs. This is crucial for populations in LMICs, where the prevalence of non-communicable diseases (NCDs), such as malnutrition, is rising rapidly and steeply [2]. By including indicators of malnutrition, food and water insecurity, and policy effectiveness, our study will highlight the need for a new framework to assess the long-term health impacts of inadequate school WaSH. By identifying risk factors of poor health literacy, our study will also address an urgent need to create evidence-based strategies aimed at promoting behavior change, i.e., hygiene practices, that can last beyond childhood and endure along the life course into adulthood.

Our study included intervention components (e.g., health education, poster-making and restroom cleaning contests, promotion of hygiene practices through behavioral reinforcement) that are likely to be operationalized at scale in similar high-risk, low-resource settings in LMICs because they were feasible, acceptable, and affordable. Our study will support using best practices in public health promotion and enhancing local research capacity. We provided local researchers with training about: community health, population-based research, and participatory research methods; assessments of child growth and cognitive development; use of noninvasive markers to evaluate hydration status.

The interpretation of our study findings will likely be limited because of bias due to the non-random recruitment of schools and non-random sampling of children, and the lack of randomization when we assigned school clusters to control or intervention arms. We used outcome measures that could increase the risk of bias by misclassifying children or not controlling for confounding. We used self-reported outcome measures to assess food insecurity and socioeconomic status. We used urine test strips to assess dehydration. However, we did not corroborate or triangulate findings with other sources of data. It is also possible that our assessment of health literacy via questionnaire would introduce bias. We will need to account for many missing responses due to children dropping out of our study because they graduated and/or transferred to a different school. We collected data on many outcomes and will likely run the risk of seeing a “multiple comparisons effect”. This may occur because as the number of outcome measurements increases, so does the tendency of seeing a false-positive [48].

### Implications for Research and Policy

More studies are needed to improve health literacy assessment, expanding its scope to include more relevant content. It would be helpful to corroborate observed handwashing with children’s self-reported handwashing, not just after using the toilet but also before eating. Another option would be to measure a handwashing-proxy, e.g., monitoring the usage of water, soap, and paper/towels in schools as an indicator of children’s handwashing. Enhanced measurement of dehydration ought to be explored by using a refractometer instead of urine test strips, and then corroborating findings with observed clinical signs of dehydration and children’s subjective report of thirst. Sound study designs are needed to improve the generalizability of findings and reduce the risk of bias. It would be helpful to randomly recruit schools and children and randomly assign school clusters to control and intervention arms. It would be useful to design a cohort study that would follow children into adulthood to gain a better understanding of the long-term effects of inadequate WaSH on human growth and nutrition status. Studies are needed to describe the relationship between schools’ menstruation management services and children’s health and education outcomes.

Our findings will demonstrate the need for improved development and enforcement of school WaSH policies, as well as health education and hygiene practices. When synthesized with data from formative research on the barriers and facilitators of handwashing and the use of school WaSH facilities, our findings will enable health practitioners, educators, and other researchers to better promote adherence to proper handwashing. Specifically, our work can inform efforts to improve hygiene education and prevent the neglect of school WaSH facilities by promoting proper operation, maintenance, cleaning, and adequate financing. Our study is very timely and relevant, offering evidence to decision-makers who are responsible for managing the safe reopening and operation of schools during the Corona disease 2019 (COVID-19) pandemic. Our results will provide support for maintaining school WaSH facilities, including water security, and above all, promoting handwashing. Threats to children’s health in relation to school WaSH have recently been exacerbated by the COVID-19 pandemic, especially in resource-constrained settings like public schools in LMICs. Urgent, evidence-based action is required to protect vulnerable populations of children in these settings where citizens face a disproportionately high risk for COVID-19-related death and disease, in addition to severe economic, environmental, and sociopolitical consequences [49,50]. The research protocol described in this paper can serve as a blueprint for future intervention studies to be conducted in other LMICs.

## 4. Conclusions

Effective school-based WaSH interventions are needed to better protect children’s health, especially in LMICs. The design of this cluster-RCT aims to measure the effectiveness of a comprehensive school-based WaSH intervention by measuring impacts on children’s health literacy, handwashing, and nutrition and comparing impacts across study arms that received different volumes (low, medium, or high) of health education. This will enable a deeper understanding about how school WaSH can be better managed to promote children’s health and prevent disease, particularly in precarious environments constrained by limited resources such as urban poor megacities in LMICs.

## Figures and Tables

**Figure 1 ijerph-18-00226-f001:**
[figure not shown]
Conceptual framework for water, sanitation, and hygiene (WaSH) and child nutrition, hydration, and cognitive outcomes. Adapted from Dearden et al. [26]. Note: body mass index-for-age z-score (BAZ), height-for-age z-score (HAZ), socioeconomic status (SES); soil-transmitted helminth (STH), water, sanitation, and hygiene (WaSH). We will analyze relationships symbolized by solid arrows, not dashed arrows. Variables that may not be available for analysis during this phase of the research project are symbolized by gray color. ^(1)^ Malnutrition status: stunted, undernourished, and over-nourished.

**Figure 2 ijerph-18-00226-f002:**
[figure not shown]
WaSH in Manila Schools project aims and timeline. Note: water, sanitation, and hygiene (WaSH). (**a**) Aims of overall project, observational study, and longitudinal study. (**b**) Timelines for observational study and longitudinal study, including research activities. ^(1)^ Please see References [27]. ^(2)^ Eight months after implementing the intervention, we revisited children from the control and intervention arms for a follow-up assessment that used the same study design as the baseline assessment. We used the same survey instruments to measure: children’s health literacy (Tables S3 and S4) and health and nutrition outcomes; children’s handwashing prevalence; school restrooms’ WaSH adequacy; and schools’ WaSH policies. ^(3)^ In November 2018, 17 months after implementing the intervention, we administered a household questionnaire for children (Table S5), some of whom had graduated and/or transferred to different schools. We completed the household questionnaire in February 2019.

